#### Statistical analysis

2.8.5

Primary analyses were conducted using the intention-to-treat (ITT) dataset, defined as the subset of participants who completed ≥1 intervention session, baseline assessment, and ≥ 1 post-baseline evaluation. In accordance with CONSORT guidelines, missing data were handled via multiple imputation (R package ‘mice’ v3.14.0). Sensitivity analyses were performed using the per-protocol set (PPS) to validate robustness.

The per-protocol set (PPS) followed ICH E9 guidelines with three integrated criteria: protocol compliance requiring 80–120% intervention dose completion, avoidance of prohibited medications, and key visit time deviations ≤3 days; data integrity enforcing <5% missingness in CDISC ODM v2.1-compliant CRF fields and laboratory CV% <15; and analytical scope restrictions that included cases with complete demographic/clinical data for baseline analysis, excluded efficacy cases with blinded-independent-adjudication-confirmed major protocol deviations (MPDs), while employing a modified PPS (mPPS) for safety analysis to retain participants discontinuing due to adverse events (AEs).

Post-trial, an independent third-party observer (uninvolved in study design or intervention delivery) performed the following: (1) Baseline data collection: Including gender, age, disease duration (months), BMI, education level, occupation category, marital status, and dietary patterns; (2) Outcome measures collection: Primary outcomes: Pittsburgh Sleep Quality Index (PSQI) and Nepean Dyspepsia Symptom Index (NDSI);Secondary outcomes: Insomnia Severity Index (ISI), 36-Item Short Form Health Survey (SF-36), inflammatory biomarkers (e.g., IL-6, CRP), and neurotransmitter levels (e.g., 5-HT, GABA); (3) Data de-identification: Removal of all direct or indirect identifiers (e.g., name, ID number), with assignment of unique study IDs.

After de-identified data underwent ETL (Extract-Transform-Load) processing for standardization, the standardized data were imported into statistical software for further analysis. Measurement data were expressed as Mean ± SD. Differences among groups were analyzed by Student *t* test or one-way ANOVA, SNK or LSD method was used for multiple comparison. Qualitative data were described as percentages and analyzed using Chi-square (*χ*^2^) test or Fisher’s exact test as indicated. The *p*-value reported was two-sided and value of less than 0.05 was considered statistically significant. All analyses were performed using the SPSS software (Version 20.0, SPSS Inc., USA).

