### Intervention

2.7

Following standardized screening, all participating clinicians underwent unified training in both taVNS and sham taVNS protocols. The informed consent form explicitly stated that the study involved two distinct neuromodulation interventions (which may differ in electrical sensation and therapeutic responses). Training modules included: (1) Device operation: standardized procedures for power cycling and locked parameter interfaces; (2) Anatomical localization: precise electrode placement at the tragus: the inferior margin of the intersection between the superior and inferior crura of the antihelix within the cymba conchae and the junction of the inferior crus of the antihelix and the auricle within the cymba conchae using auricular anatomical charts; (3) Blinding maintenance: standardized communication protocols to prevent unintentional disclosure of group allocation. All interventions were conducted in standardized treatment rooms within the hospital inpatient department.

All clinicians participating in this study were required to have at least 2 years of standardized acupuncture practice. Participants were placed in a supine position, and the auricular stimulation areas were cleaned with 75% ethanol solution followed by placement of ear clips. The clinically trained operator, blinded to group assignment, using transcutaneous auricular vagus nerve stimulators (tVNS501), precisely placed bipolar electrodes at standardized anatomical sites: the concha cymba (the inferior margin of the intersection between the superior and inferior crura of the antihelix within the cymba conchae). The intervention protocol consisted of 30-min sessions, administered weekdays from 9:00 to 11:00 AM for three consecutive weeks (15 sessions total).

Participants shall be withdrawn from the trial and provided with appropriate medical interventions under any of the following circumstances: (1) occurrence of serious adverse events; (2) voluntary withdrawal request from the participant; (3) clinical deterioration of the underlying condition; (4) requirement for prioritized treatment of other medical disorders; or (5) development of localized irritation or allergic reactions.

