##### Pittsburgh sleep quality index (PSQI)

2.8.2.1

Assessment timepoints: Baseline (T0), post-intervention (T1, week 3), and follow-up (T2, week 4 post-treatment).

Evaluation domains: Seven components including subjective sleep quality, sleep latency, and sleep duration.

Scoring system: Total scores range from 0 to 21, with ≥8 indicating sleep disturbance. A change ≥3 points was considered clinically significant.

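### The primary set labelled ITT is a modified ITT set: participants withdrawn before week 3 may leave the primary comparison for reasons tied to outcome or treatment, with bias of unknown direction

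*Protocol article*

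**What the plan says.** **Analysis set (2.8.5).** "Primary analyses were conducted using the intention-to-treat (ITT) dataset", and that set is "defined as the subset of participants who completed ≥1 intervention session, baseline assessment, and ≥ 1 post-baseline evaluation". In the same paragraph "missing data were handled via multiple imputation", and the per-protocol set is the one sensitivity set named. A modified per-protocol set keeps participants who stop because of adverse events, but for safety only.

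**Timing of the outcome (2.8.2.1, 2.8.2.2).** The PSQI schedule reads "Baseline (T0), post-intervention (T1, week 3), and follow-up (T2, week 4 post-treatment", and the NDSI follows it. The abstract places the primary endpoints at week 3. Under section 2.7 treatment is "administered weekdays from 9:00 to 11:00 AM for three consecutive weeks (15 sessions total", so every session precedes the first scheduled post-baseline efficacy score.

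**Withdrawal (2.7).** "Participants shall be withdrawn from the trial and provided with appropriate medical interventions under any of the following circumstances": five grounds follow. They include serious adverse events, "clinical deterioration of the underlying condition", and local irritation or allergy. The text speaks of leaving the trial, not only of stopping stimulation, and the article does not provide for assessing these people afterwards.

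**Sham (2.6).** The sham device touches the ear but passes no current.

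**The concern.** An ITT set contains everyone randomised, in the arm to which they were randomised. Here membership depends on events after randomisation: receiving a session and reaching a post-baseline evaluation. Such a set is common and often harmless when the exclusions have nothing to do with outcome or treatment. In this plan the withdrawal rules create a possible link to both. Deterioration is close to being the outcome itself. Irritation caused by current can arise only where current flows.

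If people leave for these reasons before week 3, the primary comparison is no longer between the groups as randomised, and the label tells readers that it is. Neither safeguard in section 2.8.5 helps. Imputation fills gaps only for people already in the set; for the week-3 endpoint that mainly means someone who missed T1 but attended T2. The per-protocol set requires at least 80% of the intervention dose, so it moves further from all randomised.

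**Working it through.** **Inputs from the protocol article.** 30 per arm, 60 in total; anticipated dropout 5-10%; anticipated response 20% on sham and 70% on active (all 2.5); a PSQI change of 3 points or more counts as clinically significant (2.8.2.1).

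**Assumed, because the article gives no such figures.** Active completers improve 4 PSQI points, sham completers 1 point, participants withdrawn before T1 0 points.

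**1. The plan's own figure.** Two-sided z-test for two proportions, unpooled variance: n = (1.960 + 2.326)² × (0.2×0.8 + 0.7×0.3) / 0.5² = 18.37 × 0.37 / 0.25 = 27.2, so 28 per group, as stated. With the pooled-variance formula, power is 0.987 at 30 per arm and 0.977 at 27 per arm (10% lost). The loss of power is small; the issue is bias.

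**2. How many could be lost.** 0.05 × 60 = 3 and 0.10 × 60 = 6. This is an upper figure: it takes all dropout to occur before T1, whereas dropout between T1 and T2 leaves a participant in the set.

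**3. Active-arm mean.** With a fraction q withdrawn at 0 and completers at 4, the mean over all randomised is 4(1 − q), and the overstatement is 4q.
- q = 5%: mean 3.8, overstated by 0.2; 0.2/3 = 7% of the threshold.
- q = 10%: mean 3.6, overstated by 0.4; 0.4/3 = 13%.

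**4. Between-arm difference.** Completers alone always show 4.0 − 1.0 = 3.0. With 10% lost:

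| Arm losing 10% | All randomised | Error in the completer estimate |
|---|---|---|
| Active only | 3.6 − 1.0 = 2.6 | +0.4 (overstated) |
| Both | 3.6 − 0.9 = 2.7 | +0.3 (overstated) |
| Sham only | 4.0 − 0.9 = 3.1 | −0.1 (understated) |

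At 5% the errors halve: +0.2, +0.15 and −0.05.

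**5. One-sided worst case on the response scale.** Suppose 1, 2 or 3 non-responders are lost from the active arm only. With 21 responders of 30, the apparent active rate becomes 21/29 = 72.4%, 21/28 = 75.0% or 21/27 = 77.8% instead of 70%. With no true effect (400,000 simulated trials), the false-positive rate in favour of active, nominally 0.025, becomes 0.031, 0.035 or 0.044 at a common response of 20%. At a common 70% it is 0.044, 0.075 or 0.124. These figures are adverse by construction, since every loss is a non-responder on active.

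**6. What imputation alone would do.** A participant withdrawn before T1 has only baseline data. By-arm imputation under missing at random draws that person's score from completers in the same arm. In step 3 it would return about 4.0, not 3.6-3.8. Widening the set without collecting scores would therefore leave the illustrated bias in place.

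**The case against.** The strongest reply is that nothing in the article shows a biased comparison, and much of that reply stands.

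- **Differential loss is not documented.** A reader might infer that the trial will lose people at different rates by arm and that this favours active. The article gives no withdrawal rates by arm or reason. Irritation losses on active would tend to flatter active, but deterioration losses on sham would flatter sham. Ear clips and ethanol cleaning are used in both arms, so irritation under sham is possible too.
- **A larger size is not supported.** A reader might take the 20% dropout figure in section 2.10 and arrive at 4 × 0.20 = 0.8 points. That figure is an emergency trigger for the monitoring board; the expected rate is 5-10%. Likewise, the 0.124 in step 5 needs three losses, all non-responders, all on active, at 70% response in both arms.
- **Post-baseline evaluation is not defined.** If a symptom diary (2.11.8) or a session safety observation (2.9.1) counts, fewer people are excluded. They would still have no PSQI or NDSI score at week 3, so the difficulty would move to the imputation in step 6.
- **Irritation may not always mean withdrawal.** Section 2.10 provides for monitoring at Grade 1 and a pause of up to 7 days at Grade 2, while section 2.7 withdraws for local irritation. The two sections conflict, so automatic loss is not established.
- **A condensed article may omit follow-up after discontinuation.** That is fair for procedural detail. It does not excuse the definition of the primary set, which the article states outright and labels wrongly.

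**Conclusion.** The point holds as a stated rule that is wrong, not as an omission. The primary set is a modified ITT set under an ITT label. Together with the week-3 first assessment and withdrawal from the trial, it may drop people for reasons related to outcome or treatment, and no other part of the article brings them back.

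The size is modest. Up to 3-6 of 60 could be lost, if all of the stated 5-10% dropout precedes T1. On the assumed changes of 4 and 0 points, the active-arm mean is overstated by 0.2-0.4 PSQI points, 7-13% of the 3-point threshold. With sham completers assumed to improve 1 point, the between-arm error runs from −0.1 to +0.4, depending on which arm loses people.

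The documents do not support the claim that the arms will differ in withdrawals, or that the result will favour taVNS. The net direction is unknown, and without scores collected after withdrawal it could not be established afterwards.

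**What to change.** 1. In section 2.8.5, define the primary set as all randomised participants, analysed in the arm to which they were randomised. Relabel the present set modified ITT and keep it as a sensitivity analysis.
2. In section 2.7, leave the stopping criteria as they are, but separate stopping stimulation from leaving the trial, so that T1 and T2 questionnaires are still collected unless consent is withdrawn. This is the step that removes the bias.
3. Apply the planned multiple imputation to the scores that remain missing. Because by-arm imputation from baseline alone would not remove outcome-related bias, add a sensitivity analysis that imputes withdrawn participants unfavourably or counts them as non-responders.
4. Reconcile sections 2.7 and 2.10 on how adverse events such as local irritation are handled.

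The cost is a few sentences and follow-up questionnaires for the few who stop. The sample size does not change. The estimate may come out less favourable. The first participant was enrolled in July 2024, so scores for anyone already withdrawn may not be recoverable; for them only the unfavourable-imputation analysis is available.

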#### Control of confounding bias

2.11.2

Confounding bias predominantly arises during data analysis due to distorted causal relationships between exposure factors and outcome variables. When confounding factors (third variables associated with both exposure and outcome) remain inadequately adjusted, erroneous causal attribution may occur, leading to overestimation or underestimation of effect sizes. This study implemented multivariable regression models (adjusting for baseline covariates such as age and gender) combined with propensity score matching to statistically control known confounders.

Additionally, sensitivity analyses were conducted to assess potential impacts of unmeasured confounders, with *E*-values quantifying the robustness of causal inferences. A prospective covariate data collection protocol (based on literature review and causal diagram analysis) further ensured systematic identification of confounding factors.

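### The per-protocol set, the only check shown that bears on withdrawal, rests on largely the same completers as the primary analysis, so their agreement cannot validate robustness to outcome-related withdrawal

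*Protocol article*

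**What the plan says.** All references are to the protocol article.

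- **Primary set (2.8.5).** The set is labelled intention-to-treat but is "defined as the subset of participants who completed ≥1 intervention session, baseline assessment, and ≥ 1 post-baseline evaluation".
- **Missing data (2.8.5).** Within it, "missing data were handled via multiple imputation", using the R package `mice`. Neither the imputation model nor the missingness assumption is stated.
- **Robustness (2.8.5).** "Sensitivity analyses were performed using the per-protocol set (PPS) to validate robustness". Membership requires, among other things, "protocol compliance requiring 80–120% intervention dose completion" and "data integrity enforcing <5% missingness" in the case report form fields.
- **Withdrawal (2.7).** Participants leave the trial, not only the treatment, for several reasons. Two of them are "clinical deterioration of the underlying condition" and "development of localized irritation or allergic reactions".
- **Assessment times (2.8.2.1, 2.8.2.2).** PSQI and NDSI are scheduled at baseline (T0), week 3 (T1) and follow-up (T2). The Abstract sets the primary endpoints at week 3.
- **Other sensitivity work (2.11.2).** "sensitivity analyses were conducted to assess potential impacts of unmeasured confounders", with E-values. This concerns confounding, not missing outcomes.

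**The concern.** A sensitivity analysis tests an assumption only if it changes that assumption. The assumption in question is that participants who left the trial would have scored like comparable participants who stayed. Some withdrawal reasons in section 2.7 make this doubtful: deterioration is close to the outcome itself, and a skin reaction may depend on the arm.

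The per-protocol set does not relax the assumption. It selects on completing treatment and having nearly complete data. Section 2.8.5 recognises this for safety, where a modified per-protocol set keeps those who stop because of adverse events. It makes no matching provision for efficacy.

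At stake is how the result is read. Two analyses of nearly the same completers will tend to agree whether or not withdrawal was related to outcome, and the plan would report that agreement as robustness.

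**Working it through.** **1. The plan's own figure.** The plan gives no number for this point. Its sample size (2.5) sets the arm size used below. With a two-sided unpooled z-test, 20% against 70%, α = 0.05 and power 0.99:

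n = (1.960 + 2.326)² × (0.7×0.3 + 0.2×0.8) / 0.5² = 18.37 × 0.37 / 0.25 = 27.2, so 28 per arm, as stated.

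28/0.95 = 29.5 gives the planned 30 per arm (28/0.90 = 31.1 would give 32). The expected 5–10% dropout is 1.5 to 3 participants per arm of 30.

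**2. Who is in which set at week 3.** The dose rule means at least 0.80 × 15 = 12 sessions.

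| Participant | Primary set | Per-protocol set |
|---|---|---|
| Withdrawn before T1, no exit assessment | Out: no post-baseline evaluation | Out: T1 and T2 data missing, often too few sessions |
| Withdrawn before T1, unscheduled exit assessment | In: week-3 score imputed | Normally out, same reasons |
| Withdrawn after T1 | In: week-3 score observed | Depends on the other criteria |

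The documents schedule no exit assessment, so the first row is the usual case for early withdrawal. Those participants are missing from both analyses.

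**3. Size in PSQI points.** Let k of 30 participants in an arm be d points worse than the analysis assumes. The arm difference then shifts by (k_active/30) × d_active − (k_sham/30) × d_sham. A positive value means the analysis flatters taVNS.

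- 3 active, 0 sham, d = 3 (the plan's clinically significant change): 0.10 × 3 = 0.3
- 0 active, 3 sham, d = 3: −0.3
- 3 active, 3 sham, d = 3: 0.3 − 0.3 = 0
- 6 active, 0 sham, d = 3: 0.20 × 3 = 0.6
- 6 active, 0 sham, d = 5: 0.20 × 5 = 1.0

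Six of 30 is 20%, the level above which section 2.10 calls a DSMB session. It is not an expected rate. The value d = 5 is an assumption.

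For scale, the smallest significant difference with 27 per arm is 2.007 × SD × √(2/27). This is 1.64 points for SD 3 and 2.18 for SD 4. The documents give no SD, so both are assumptions.

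**4. Do the two analyses agree when both are biased?** Simulation with 30 per arm, no true effect, outcome SD 1, baseline correlation 0.5 and 4,000 runs. The worst scorers withdraw. Imputation uses baseline and arm under missing at random, and the per-protocol set drops those who withdrew.

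| Loss, active / sham | Bias, imputed | Bias, per-protocol | Correlation | Per-protocol rejection at 5% |
|---|---|---|---|---|
| 3 / 0 | +0.14 SD | +0.18 SD | 0.99 | 12.7% |
| 0 / 3 | −0.14 SD | −0.19 SD | 0.99 | 11.6% |
| 3 / 3 | 0.00 SD | 0.00 SD | 0.99 | 8.8% |
| 6 / 0 | +0.27 SD | +0.35 SD | 0.99 | 29.3% |

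The two estimates move together whether bias is present or absent. The imputed column assumes that withdrawn participants are in the primary set. If they are outside it, as in the first row of step 2, the primary estimate becomes the completer estimate and agreement is close to automatic.

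**5. Worst-case check at the planned effect.** All missing active participants count as failures and all missing sham participants as successes (Fisher's exact test).

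- 3 missing per arm: 19/27 vs 5/27 becomes 19/30 vs 8/30, p = 0.009.
- 6 missing per arm: 17/24 vs 5/24 (p = 0.001) becomes 17/30 vs 11/30, p = 0.20.

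**The case against.** **An analysis that varies the missing-data assumption may be in the SAP.** The SAP is not shown and an article condenses, so the absence of that analysis is no finding. What stands is narrower: the text assigns the per-protocol set the task of validating robustness, and for withdrawal it cannot do that.

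**The wording is conventional and does not mention withdrawal.** That is fair. However, the sentence directly follows the one on missing data, and no other check shown touches the issue, so a reader will take it that way.

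**The root fault is the definition of the primary set.** This is partly right. A reader might infer that the primary analysis imputes withdrawn participants and the per-protocol set then removes them. The text does not support that for most early withdrawals, because they never enter the primary set. Correcting the set alone would still leave the per-protocol analysis as the only check.

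**The direction is unproven.** This stands in full. A reader might infer that the error favours taVNS because local reactions need current. Section 2.7 does not limit the criterion to reactions to current, and describes ethanol cleaning and ear clips without distinguishing arms. Sham devices also stay in contact with the ear (2.6). If taVNS works, deterioration could fall more on sham, which would bias against taVNS.

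**The effect is small at expected dropout.** This also stands: 0.3 points against a threshold of about 1.6–2.2, and p = 0.009 in the worst case at the planned effect.

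**Conclusion.** The point holds in a limited form. For withdrawal and missing outcomes, the per-protocol set is the only check shown. It conditions on largely the same completers as the primary analysis, so agreement between them cannot show that outcome-related withdrawal left the PSQI and NDSI results unbiased.

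It would be too strong to call it the plan's only sensitivity analysis, since section 2.11.2 adds E-values, although these do not address missing outcomes. It would also be too strong to predict bias in favour of taVNS. Bias needs a difference between arms in outcome-related loss, may go either way, and is near zero with equal loss.

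The size is about 0.3 PSQI points at 10% one-sided loss and a 3-point shortfall, and 0.6–1.0 at 20% one-sided loss with shortfalls of 3–5 points. The comparison threshold rests on assumed SDs of 3–4, and the simulation on strict withdrawal of the worst scorers. The issue matters most for a modest treatment effect, unequal withdrawal or dropout near 20%. It is a cheap improvement worth making, not a flaw that undermines the trial.

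**What to change.** Keep the per-protocol analysis as supplementary and delete the statement that it validates robustness. As the sensitivity analysis for PSQI and NDSI at T1:

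1. Include all randomised participants and impute missing week-3 scores with `mice`, with arm and baseline score in the model.
2. Shift the imputed scores in steps, separately by arm. For example, use 0 to 5 PSQI points and, in proportion to scale length (5/21 × 16 = 3.8), about 0 to 4 NDSI points. Include the case where only active-arm scores are made worse. A reference-based version, imputing active-arm withdrawals from the sham arm, is optional.
3. Pool by Rubin's rules and report the shift at which the conclusion changes, so that readers can judge whether it is plausible.
4. Report withdrawals by arm and reason beside it, since imbalance drives the bias.

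The cost is one paragraph of text and a few lines of R in a package already named. No new data or participants are needed, and the withdrawal criteria are untouched. The downside is slightly more analysis work and a result that may look less robust.

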##### Inflammatory biomarkers

2.8.3.3

Assessment timepoints: Consistent with the aforementioned schedule (T0-T1).

Analytical method: Serum concentrations of IL-1*β*, IL-4, IL-6, TNF-*α*, hs-CRP, and TGF-β were quantified using enzyme-linked immunosorbent assay (ELISA).

Blood sampling protocol: Venous blood samples were collected at T0 (baseline) and T1 (post-intervention) under morning fasting conditions (≥8 h overnight fast).

Interpretation criteria: Concentrations were reported in pg/mL. Biological significance was defined as >15% change from baseline.

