##### Neurotransmitter metabolomics profiling

2.8.3.4

Assessment timepoints: Consistent with the aforementioned schedule (T0-T1).

Analytical platform: Separation was performed using an Agilent 1,290 Infinity LC system coupled with a 5,500 QTRAP mass spectrometer (SCIEX) operated in negative ion mode.

Blood sampling protocol: Venous blood samples were collected at T0 (baseline) and T1 (post-intervention) under morning fasting conditions (≥8 h overnight fast).

Analytes:

Monoamines: DA, 5-HT, NE.Amino acids: Glu, GABA.

Interpretation criteria: Pearson correlation analysis was performed to assess the association between dynamic changes in neurotransmitter levels and improvement magnitudes of PSQI/NDSI scores, with |*r*| ≥ 0.3 defined as significant correlation (two-tailed test, *p* < 0.05).

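### Laboratory CV below 15% is written into the per-protocol set definition, so precision of secondary biomarker assays can decide who enters the robustness check on PSQI and NDSI

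*Protocol article*

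**What the plan says.** Section 2.8.5 (Statistical analysis) of the protocol article bases the primary analyses on the ITT dataset and gives the PPS its role: "Sensitivity analyses were performed using the per-protocol set (PPS) to validate robustness". It then defines the set: "The per-protocol set (PPS) followed ICH E9 guidelines with three integrated criteria".

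- **First criterion:** compliance, covering dose completion of 80–120%, prohibited medication, and visit deviations of at most 3 days.
- **Second criterion:** "data integrity enforcing <5% missingness in CDISC ODM v2.1-compliant CRF fields and laboratory CV% <15".
- **Third criterion:** scope by type of analysis. For efficacy it "excluded efficacy cases with blinded-independent-adjudication-confirmed major protocol deviations (MPDs").

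The same section names PSQI and NDSI as primary outcomes and lists the inflammatory and neurotransmitter measures as secondary. Sections 2.8.3.3 and 2.8.3.4 have both groups of biomarkers measured at T0 and T1 only. Section 2.11.6 (Laboratory quality assurance) refers to ISO 15189:2022 and laboratory operating procedures. It does not mention a CV limit.

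**The concern.** A PPS is a set of participants, and its membership rules should reflect whether each person received and completed the trial as planned. Assay CV is a property of a measurement. It belongs to replicates of a sample or to a run, and it carries no information on adherence or on the quality of a questionnaire score.

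Because the limit sits inside the set definition and is joined to a completeness rule, it can remove people from the PSQI and NDSI sensitivity analysis for reasons unrelated to either scale. A difference between the ITT and PPS results could then reflect assay losses and not non-adherence, and agreement would be harder to interpret.

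The wording also leaves open which analyte counts, whether the CV is within-sample or between-run, and how many failures matter. Two statisticians could therefore build different sets from the same data.

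**Working it through.** The plan derives no figure from the 15% limit, so there is nothing of its own to reproduce. The check has two parts: what the text does, and how large the effect might be.

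**1. The text.** The CV limit is part of the second of three criteria that define the PPS. The PPS is the sensitivity set for the primary analyses. The primary outcomes are questionnaires. The third criterion distinguishes baseline, efficacy and safety analyses, but does not restrict the CV limit to biomarkers, and neither does 2.11.6. Two readings are possible:

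- *Per sample:* a participant with all 15 sessions and complete PSQI and NDSI can be excluded because of one biomarker result.
- *Per run:* a failed run excludes everyone on it, or the limit has no effect on membership and does not belong in the definition.

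The wording needs correcting under either reading.

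**2. Number of results per participant.** Inflammatory analytes (2.8.3.3): IL-1β, IL-4, IL-6, TNF-α, hs-CRP and TGF-β, so 6. Neurotransmitters (2.8.3.4): "Monoamines: DA, 5-HT, NE.Amino acids: Glu, GABA", so 5. Two sampling times. (6 + 5) × 2 = 22.

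**3. Illustration by failure rate.** Assume that results fail independently with probability p, that any one failure excludes, and that nothing is re-run. Share retained = (1 − p)^22, applied to the planned 60:

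| p (assumed) | (1 − p)^22 | Retained of 60 |
|---|---|---|
| 1% | 0.80 | about 48 |
| 2% | 0.64 | about 38 |
| 5% | 0.32 | about 19 |
| 10% | 0.10 | about 6 |

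**4. Illustration by assay precision.** Assume duplicates with true CV c. The observed CV of a pair is |x1 − x2| / (√2 × mean), so P(CV > 15%) ≈ 2 × [1 − Φ(0.15/c)]. With 22 independent results and exclusion on any failure:

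| True CV (assumed) | P(one result fails) | P(at least one of 22 fails) | Retained of 60 |
|---|---|---|---|
| 4% | 0.0002 | 0.4% | 59.8 |
| 5% | 0.0027 | 5.8% | 56.5 |
| 6% | 0.0124 | 24% | 45.6 |
| 8% | 0.0608 | 75% | 15.1 |
| 10% | 0.1336 | 96% | 2.6 |

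The loss runs from negligible to almost total over a narrow range of precision. The document gives neither replicate numbers nor assay precision, so it does not place the trial anywhere in this range.

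**5. Dependence on concentration.** If assay noise has an additive part, CV = √(a² + (b·m)²)/m at concentration m. With assumed a = 0.1 and b = 0.05 (arbitrary units), m = 1 gives CV 11% and an 18% chance of failing; m = 8 gives CV 5% and 0.4%. This shows that loss related to biomarker level is possible in principle. No input to it comes from the document.

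**6. After the change.** With the limit applied only to biomarker results, it removes 0 of 60 participants from the PSQI and NDSI PPS, whatever the assay precision.

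**The case against.** The strongest reply is that the sponsor probably meant an ordinary laboratory acceptance limit. The phrase stands under data integrity, in a sentence that mixes membership rules with data standards and analysis scope. Assays are placed under ISO 15189 and operating procedures elsewhere. The explicit efficacy exclusion is for adjudicated major deviations, and the text does not call a CV failure one of these. How a CV limit is applied is also a detail that a full protocol or SAP may settle. The PPS is only a sensitivity set, and it already conditions on other post-randomisation events.

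Much of this stands. The intent may well be benign, the unit of the CV is not given, and exclusion on any one of 22 results is an assumption. But the article does state the limit as part of a PPS criterion and does not confine it to biomarkers. That is a rule stated in the wrong place, and not merely a missing detail.

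Two stronger readings are tempting, and the document supports neither:

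- **That the rule would preferentially drop participants with low cytokines, and so more of the active arm at T1.** This would need a within-sample CV, values near the assay floor, a sufficient fall in cytokines over three weeks, and no re-run. The document gives no replicate numbers, quantification limits or expected concentrations. Under the per-run reading, exclusion follows the run and not the participant's own level, so the argument largely disappears. Ten of the 22 results are mass-spectrometry neurotransmitters, to which reasoning about ELISA does not apply.
- **That the PPS will shrink sharply.** It could, but with precise assays the loss is trivial, and correlated failures or repeat assays would reduce it further.

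**Conclusion.** The point holds as a defect in the PPS definition. As written, assay precision for secondary biomarkers can determine who enters the robustness check on two questionnaire outcomes that need no assay. The primary ITT analysis is untouched, so the consequence is confined to the interpretation and reproducibility of the sensitivity analysis.

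The size is unknown. The 80% to 10% retention range rests on assumed failure rates of 1% to 10%, independence, exclusion on any failure, and no re-runs. It is illustrative and not a forecast. Preferential loss by cytokine level or by arm remains a hypothetical possibility that the document does not show. The case for changing the wording depends on neither.

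**What to change.** Delete the CV limit from the PPS membership criteria in 2.8.5. State it instead as a validity rule for each biomarker result: after any repeat that the laboratory procedures already provide, a result that still fails is flagged or set to missing for that analyte and visit only. PPS membership for PSQI and NDSI then rests on dose completion, prohibited medication, visit timing, CRF completeness and adjudicated major deviations.

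If biomarker results count as CRF fields, which the article does not say, add that values set to missing for assay reasons do not count towards the 5% missingness limit. Otherwise the same exclusion could return by that route.

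The cost is about one sentence in the analysis-set definition, with no new data and no loss of the laboratory standard. It should be settled before unblinding, so that the set is not defined with results in view.
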